**Discussion:**

We hypothesize that practice facilitation will result in superior clinical outcomes compared to usual care; that the effects of practice facilitation will be mediated by greater adoption of system changes in accord with PCMH and CCM; and that there will be increased adaptive reserve and change capacity.

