### Intervention components

#### Practice facilitation protocol

The duration of the intervention is 12 months for each wave, and it is being implemented at the site level. PF comprises the following components: (1) onsite visits by the practice facilitator with the medical director and/or staff twice in the first month and then monthly thereafter; (2) expert consultation (i.e., quarterly webinars and “ask the expert” email consultant service); and (3) facilitated opportunities for shared learning across intervention sites (e.g., peer-to-peer collaborative calls) [8]. The practice facilitator’s main role is to coordinate and facilitate meetings with study sites and to assist primary care practices in setting practice change and performance goals and in developing strategies for implementing evidence-based components of the models for practice transformation, including CCM, PCMH, and Bodenheimer’s 10 building blocks of primary care [9, 10, 33]. For this purpose, a quality improvement (QI) manual informed by these models was developed by PCIP to drive delivery of the intervention. PFs also share best practices across sites, train practice staff on QI processes and methods to help them develop robust QI capacity (e.g., workflow mapping, generating performance reports), assist teams in testing system changes and interpreting outcomes, and assist with generating data for performance feedback and Plan-Do-Study-Act (PDSA) cycles. The practice facilitator conducts phone and email exchanges with the sites as needed between site visits during the 12-month intervention period.

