### Process evaluation measures and data collection methods

The process evaluation will have four components: internal practice context; external healthcare context; implementation fidelity; and cost (see Table 3).

**Table 3 Tab3:** Process measures, data sources and timeline for data collection

Domain	Measures	Data sources	Administration
Internal practice-level context	• Staffing/FTEs • Payer mix • Patient demographics • Baseline integration practice transformation components (population management) • PCMH certification	• Practice survey • Site visits and key informant (KI) interviews with sample of providers and staff	• Surveys at baseline, 12 and 18 months • Site visits and KI interviews baseline and 12 months
External context	• Regulatory and financial environment (e.g., pay-for-performance, value based payment)	• Provider surveys • KI interviews with sample of practice site providers and staff	• Ongoing
Implementation fidelity	• PF activities: dose, intensity and mode of delivery of PF intervention Practice change: Extent to which practice change components are implemented and in use	• PF activities: Web-based PF tracking system, Webinar registration and evaluation and collaborative call attendance • Practice change: practice change survey and site visits/KI interviews	• Ongoing PF tracking using saleforce.com • Practice change survey monthly
Cost	• Implementation and intervention cost	• Cost data collection template embedded in PF tracking system	• Ongoing and reviewed monthly

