#### Internal and external context

These domains will be assessed using both qualitative and quantitative data. The lead clinician or lead practice administrator will be asked to complete a survey (in addition to the survey described previously to assess primary care capacity) that will assess practice characteristics (e.g., use of EHR, FTEs, PCMH status, patient demographics). The survey will be conducted at baseline, 12 and 18 months. In order to obtain a deeper understanding of internal and external context, we will conduct semi-structured interviews with at least one provider and one staff person at 40 sites spread over different waves. We will visit half of these sites early in their implementation of the intervention and again toward the end of the intervention period. The interviews will focus on the practice-specific context, the local and state health policy environment, and experience with practice facilitation. We will visit the other 20 sites one time post-intervention. These sites will be chosen to represent variability in response to the intervention in terms of changes in patient outcomes.

To gain a broader perspective on external health care context and ongoing and emerging practice transformation programs in New York State and nationally, we will conduct semi-structured interviews with 10 key informants who represent leaders in this area from the city and state.

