#### Implementation fidelity

We will assess two core measures of fidelity: (1) PF activities (i.e., to what extent is the PF protocol adhered to in terms of practice visits and provider participation in webinars and collaborative calls?) and (2) practice change (i.e., to what extent is the change package, defined primarily by CCM and PCMH, implemented as specified?).Practice facilitation activities: The primary outcome measure for PF activities is the frequency, duration, and mode of contact. PF activities are measured with data from the web-based software tool (Salesforce.com) that PCIP is currently using to track their practice facilitators’ activities. Each site has a separate page in Salesforce that includes the relevant elements for documenting PF activities and practice change components. Practice facilitators complete documentation in Salesforce after every visit including the time spent at the practice site, who the practice facilitator met with at the sites, what activities were discussed, outcomes of the visits, and agreed upon next steps (e.g., set date for upcoming visit). We will also track provider participation in other components of the PF intervention (e.g., webinars).Practice change: We will also use Salesforce to assess our targeted practice changes (e.g., use of clinical decision support). Practice facilitators complete a survey, which is embedded in Salesforce, after each visit (i.e., monthly). The survey uses a 6-point scale (not yet educated; educated/PDSA; educated/using; educated/not using/deferred; educated/not using/refused; and not applicable) to assess practice change components that are the target of the intervention and correspond to the main elements of PCIP’s QI manual, which we have mapped to CCM and PCMH [9, 10]. Facilitators will also complete monthly narrative reports that will provide an overview of all implementation activities, including perceptions about what components of the intervention did and did not work and approaches to adaptation of intervention components.

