We will identify baseline organizational characteristics (e.g., site level adaptive reserve, organizational change capacity) that are associated with primary outcomes. This will be accomplished by including separately each organizational characteristic in the main models used under Aim 1 as a main effect and in interactions with the PF indicator. We will conduct a further analysis to explore the possibility that changes in organizational level factors mediate the effect of the intervention on the primary compliance outcomes. Mediation analysis methods in the context of a stepped-wedge design have not been well developed. We will conduct a preliminary analysis to assess if the intervention is associated with changes in site level adaptive reserve, organizational change capacity, and practice changes (assessed with the practice change survey). If there is a detectable effect of the intervention on the organizational level factors, we will assess whether the changes in these organizational level factors are associated with changes in the primary compliance outcomes using the Baron and Kenny “product method” as a starting point of the analysis [38]. If necessary, we will explore more complex structural equation models (SEM) adapted for Poisson outcomes as well as more recently developed causal inference mediation methods to evaluate the mediation.

#### Aim 3

We will use qualitative methods to conduct a more in-depth assessment of internal and external context including barriers and facilitators (among high and low performers) to implementing practice change and achieving ABCS outcomes. The transcriptions of the interviews and focus groups will be coded using Atlas.ti. The coding scheme will be developed by the evaluation team to focus on key dimensions identified both a priori (i.e., from the interview and focus group protocols) and those that emerge during site visits, interviews, and focus groups. Two coders will independently code at least 10 interviews and all focus groups. Double coding will continue until adequate inter-rater reliability is achieved.

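### The practice change mediator in Aim 2 has no usual-care measurement, so the effect of facilitation on it cannot be estimated against usual care

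*Protocol article*

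**What the plan says.** The Abstract (Discussion) hypothesizes that "the effects of practice facilitation will be mediated by greater adoption of system changes in accord with PCMH and CCM". The Analysis plan, Aim 2, sets out how this will be examined. A preliminary analysis tests whether the intervention is associated with changes in adaptive reserve, organizational change capacity and "practice changes (assessed with the practice change survey". If an effect is detected, a second step relates change in these factors to change in the primary outcomes, starting from the product method.

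The survey is described under Implementation fidelity: "Practice facilitators complete a survey, which is embedded in Salesforce, after each visit (i.e., monthly". The Practice facilitation protocol defines the visits as "onsite visits by the practice facilitator with the medical director and/or staff twice in the first month and then monthly thereafter", within a 12-month intervention. Table 3 gives the schedule as "Practice change survey monthly" and lists no baseline, control-period or follow-up administration. The survey has six response categories. Five are worded by whether the site has been educated, beginning with *not yet educated*; the sixth is *not applicable*.

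**The concern.** A test of whether facilitation changes a mediator needs that mediator measured both under facilitation and under usual care. Here the named instrument exists only where facilitation is under way, is filled in by the person delivering it, and uses a scale largely anchored on contact with that person. The stated test and the stated data collection do not fit together.

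Of the three mediators, this one measures adoption of system changes most directly: the article maps the survey's components to the chronic care model and the patient-centered medical home. A positive first step could be reported as evidence that facilitation changed practice systems relative to usual care, when no usual-care comparison was made.

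**Working it through.** The article gives no figure for the mediation analysis, so there is none to reproduce. The check has four parts.

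**1. Scheduled records.** Table 1 has 80, 70, 70 and 70 sites in waves 1 to 4, with 1, 2, 3 and 4 control quarters. Every wave has 4 intervention and 2 follow-up quarters.
- Control: 80×1 + 70×2 + 70×3 + 70×4 = 80 + 140 + 210 + 280 = 710 site-quarters.
- Intervention: 290×4 = 1160 site-quarters.
- Follow-up: 290×2 = 580 site-quarters.
- Facilitator visits per site: 2 in month 1 plus 11 monthly visits = 13, all within the intervention.
- Practice change survey records scheduled in control quarters: 0 of 710.

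**2. Identification.** Aim 2 does not write out the mediator model, so the fixed effects of model (1) under Aim 1 serve as illustration: intercept, t, I(PF) and I(PF)×(t − s).
- Control and intervention quarters together: rank 4 of 4.
- Intervention quarters only: I(PF) = 1 in every row and duplicates the intercept, giving rank 3 of 4 (2 of 3 without the growth term).

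The level effect β2 is therefore not estimable, and neither is a contrast such as β2 + 3β3. What can be described is how the score moves during facilitation. The result does not depend on this particular model, since any PF-versus-usual-care contrast needs usual-care records.

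**3. Other sources of practice change data.** Table 3 also lists "Practice change: practice change survey and site visits/KI interviews". Those visits and interviews are qualitative and cover 40 sites. Of these, "We will visit half of these sites early in their implementation of the intervention and again toward the end of the intervention period"; the other 20 are visited once, after the intervention. None of this supplies a usual-care measurement. By contrast, adaptive reserve and change process capacity come from provider and staff surveys with a stated baseline (Table 2).

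**4. What would follow if the gap were filled.** A small simulation scored control quarters 0 (*not yet educated*), scored intervention quarters on an arbitrary positive distribution, and gave the mediator no true effect on the outcome. It assumed 50 eligible patients per site-quarter, a 20% baseline rate and site variance 0.10. Within-site linear models on the log rate with cluster-robust standard errors stood in for the Poisson mixed model. There were 300 data sets per scenario.

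| Direct PF effect on log rate | First step significant | Both steps, adjusted for PF | Both steps, not adjusted for PF |
|---|---|---|---|
| 0 | 100% | 7.3% | 6.3% |
| 0.1 | 100% | 5.3% | 16% |

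The Monte Carlo error at a 5% rate is √(0.05×0.95/300) ≈ 1.3 points. The 100% follows from the imputed zeros and shows only that the first step then screens nothing out. The joint test adjusted for PF is close to nominal. Without that adjustment and with a direct effect it is inflated, but far from certain to reject.

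**The case against.** A reader might infer that the whole mediation test is positive by construction, so that mediation would be reported whatever facilitation achieved. The documents do not support that. A detectable effect on the mediator only opens the second step, which needs an association with outcomes extracted from the EHR through the Hub, not recorded by facilitators. Nor is the first step automatic as written: an effect that is not identified becomes automatic only if someone fills in the control quarters or reads the rise during facilitation as the effect, and the article states neither.

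Three further points on the other side have weight.
- The scoring rule is not given, and an article may leave it to the full protocol or SAP. The scale includes categories for sites that were educated but deferred or refused, so a score counting components in use need not rise with contact alone. This is why the statement about exposure to the facilitator must stay conditional.
- Aim 2 presents the mediation work as exploratory and admits that methods for stepped-wedge designs are not well developed. The Conceptual framework runs the effect through adaptive reserve and change process capability, and both of these have a baseline.
- Aim 3 already treats the survey as a component of fidelity and plans to relate fidelity to the primary outcomes.

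These limit the scope but do not remove the point. The mismatch lies between a named instrument, its stated completer and schedule, and a stated test; it is not a matter of omitted detail. Treating the first visit's record as a baseline does not help, because it is completed after contact with the facilitator has begun and does not separate facilitation from calendar time.

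**Conclusion.** The point holds for one of the three mediators. With 0 of 710 control site-quarters scheduled for the practice change survey, the intervention-to-mediator step cannot be estimated as a PF-versus-usual-care contrast. If it is carried out by reading the within-facilitation rise as the effect, or by scoring control quarters as not yet educated, it largely reflects exposure to the facilitator. Mediation through practice change would then rest on an association within the intervention period, without a randomized comparison behind it.

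The four primary analyses are untouched, and so is the first step for the other two mediators as far as this defect goes. The conclusion assumes that the survey is given only as the article describes, at facilitation visits, and that *educated* means educated by the facilitator, as the context suggests. The simulation shows direction only. The plan should be corrected before analysis.

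**What to change.** Remove the practice change survey from the intervention-to-mediator step of Aim 2. Keep it for fidelity or dose-response analyses within intervention quarters, as Aim 3 already foresees, and state that such an association is not evidence of mediation relative to usual care.

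For the first step, use the practice survey completed by the lead clinician or administrator, wherever its items on transformation components overlap with the targeted practice changes: "The survey will be conducted at baseline, 12 and 18 months". Put calendar time in that model.

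The cost is a change of analysis wording and the use of data already being collected. The downsides should be stated with it:
- The practice survey has three time points and is described mainly as a measure of context. It may cover only some of the components in the QI manual, so the mediation claim becomes narrower.
- The article does not say whether its time points run from each wave's own start. If they do, Table 1 puts the last control quarters at months 6, 9, 12 and 15 and the last intervention quarters at months 18, 21, 24 and 27. Baseline and 12-month records would then not overlap in calendar time, and the adjustment would lean on the assumed form of the trend.

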## Discussion

Half of the US adult population has one or more preventable risk factors for cardiovascular disease (CVD) including hypertension (HTN) and hyperlipidemia, but only 10 % are meeting all of their clinical goals [39]. As a result, CVD remains the number one cause of death in the US [40]. A recent analysis by Farley and colleagues concluded that optimal implementation of clinical guidelines for treating HTN and hyperlipidemia could prevent up to 100,000 deaths per year [41]. Yet, less than half of the patients with one or more CVD risk factors are receiving guideline recommended care [42–45].

HHNYC aims to fill this current research-to-practice gap by evaluating the effectiveness of practice facilitation as a quality improvement strategy for implementing evidence-based guidelines for reducing CVD-related risk factors in primary care practices in New York City. The specific focus is to improve adherence to the ABCS, with a long-term goal of creating a robust infrastructure to disseminate and implement patient-centered outcomes research (PCOR) findings in primary care practices and improve practices’ capacity to implement other PCOR findings in the future.

The study findings have the potential to accelerate the tempo of implementation and dissemination of evidence-based strategies for addressing CVD risk factors in primary care settings serving populations with higher risks of CVD-related mortality.

There are several potential methodological challenges that may be encountered during the project. First, obtaining high survey response rates from the providers can be challenging. The project team has extensive experience conducting provider surveys with the target study sites with good results. We will incorporate several strategies that have been effective in previous research in the current study sites including using financial incentives [46, 47]. Second, it is likely that we will observe variation in implementation fidelity. We have defined the core elements of the intervention; however, based on our previous experience and review of the current implementation literature, we acknowledge that adaptations to the unique practice context will be necessary. This is an inherent component of practice facilitation and is meant to enhance adoption and sustainability. We will use rigorous methods to measure implementation fidelity of core elements and will also document adaptations to enhance external validity. Finally, unforeseen changes in the external context of health care delivery may affect implementation outcomes (e.g., changes in Medicaid reimbursement). The practice context in NYC is similar to that nationally, with simultaneous implementation of numerous practice transformation programs and projects. Notable statewide activities include the Medicaid PCMH incentive program to expand primary care capacity and improve care coordination, especially for patients with chronic disease; support of two state-designated regional extension centers to promote adoption of electronic health records (EHRs); the Medicaid and Medicare meaningful use incentive programs; and, recently, the $6 billion Delivery System Reform Incentive Payment Program (DSRIP), which creates new regional collaborations to reduce avoidable hospitalizations among Medicaid patients [48, 49]. Programs and funding related to practice transformation will continue to evolve. Our plan to collect data on external context via key informant interviews with Steering Committee members and pre and post intervention provider surveys will allow us to analyze for any historical threats to internal validity.

## Abbreviations

ABCS, aspirin, blood pressure, cholesterol, smoking cessation; AHRQ, Agency for Healthcare Research and Quality; CCM, chronic care model; CFIR, Consolidated Framework for Implementation Research; CVD, cardiovascular disease; EBPG, evidence-based practice guidelines; EHR, electronic health records; FTE, full-time equivalent; GLMM, generalized linear mixed model; HHNYC, HealthyHearts New York City; NYC, New York City; NYCDOHMH, New York City Department of Health and Mental Hygiene; NYUSOM, New York University School of Medicine; PCIP, Primary Care Information Project; PCMH, patient-centered medical home; PCOR, patient-centered outcomes research; PDSA, Plan-Do-Study-Act; PF, practice facilitation; QI, quality improvement; SEM, structural equation models

## Appendix

### Power/effect size analysis

With the pre-specified number of sites (250) and design (wedge design with four strata starting 3 months apart, we investigate the intervention effects under each of the primary hypotheses in Aim 1, that are detectable with at least 80 % power of a two-sided significance test with *α* = 0.05. Conversely, we assess the power to detect effects that are clinically meaningful and realistic.

For each of the four outcomes, we are interested in comparing the proportion of eligible patients in a physician’s panel who meet compliance (i.e., appropriate blood pressure level, appropriate cholesterol level, indication that aspirin was recommended, and indication of referral for smoking cessation) in the third quarter after PF intervention with the compliance proportion at baseline. In particular, we are interested in the difference *d*
_*π*_ = *π*
_3_ − *π*
_0_, where *π*
_0_ is the baseline compliance rate, and *π*
_3_ is the third period compliance rate. The proportions *π*
_0_ and *π*
_3_ will be estimated by *C*
_0_/*E*
_0_ and *C*
_3_/*E*
_3_, respectively, where *C* is the number of patients in compliance and *E* is the number of eligible patients. We will use the model to estimate the difference *d*
_*π*_. However, because of the specific Poisson distributions of the data and the model that we will be using, the treatment effect is more naturally expressed as a ratio rather than a difference: *r*
_*π*_ = *π*
_3_/*π*
_0_.

We conducted the simulations varying the ratio *r*
_*π*_, but for the clarity of interpretation, we also present the effect as a difference *d*
_*π*_. Our goal is to find the *r*
_*π*_ ’ s (and *d*
_*π*_ ’ s) that would allow 80 % power of a two-sided test for significance with *α* = 0.05. We simulate the outcomes based on different assumptions about baseline compliance rates, random effects (which are at the scale of log(*C*)), and patient eligibility numbers. For each set of assumptions, 2000 data sets were generated using the GLMM model given in Eq. (2).

2 $$ \log \left({C}_{jt}\Big|{d}_j\right)=\mu +{\beta}_1t+{\beta}_2{I}_{jt}^{\mathrm{PF}}+{\beta}_3{I}_{jt}^{\mathrm{PF}}\left(t-{s}_j\right)+\gamma {Z}_j+{d}_j+ \log \left({E}_{ijt}\right), $$

The rate ratio *r*
_*π*_ is a function of baseline treatment effect (*β*
_2_) and time-related treatment effect (*β*
_3_) : *r*
_*π*_ = exp(*β*
_2_ + 2*β*
_3_). For each of the 1000 data sets, we estimated the same model and tested the hypothesis that *β*
_2_ + 2*β*
_3_ (the effect size in the third quarter) was significantly different from 0. The proportion of significant results represented the power of the study under the specific set of assumptions.

For the purposes of simulation, we assumed 63 sites in each stratum, for a total of 252 sites. Preliminary simulations indicated that larger general time trends (*β*
_1_) and larger number of patients in a physician panel both increased power. Based on this, our final simulations included very conservative assumptions of zero growth trend (*β*
_1_ = 0) and average eligibility size (*E*
_*jt*_) of 50 patients per physician at the practice. In the simulation, a general level of *E*
_*j*_ for site *j* was generated from a Poisson distribution of mean 50 × the number of physicians at the site. The value of *E*
_*jt*_ for a particular time period was calculated (and rounded to the nearest integer) as *E*
_*ij*_ + *e*
_*ijt*_, where *e*
_*ijt*_ ~ *N*(mean = 0, sd = 2). For each site *j* during period *t*, log(*C*
_*jt*_) was generated using equation (2). A value *C*
_*jt*_, the number of patients in compliance for site *j* during period *t* was generated from a Poisson distribution with mean *C*
_*jt*_.

Table 4 shows results after varying effect size parameters (*β*
_2_ & *β*
_3_), baseline compliance rate (*π*
_0_), site-level random effect variance (*σ*
_*d*_^2^), and patient eligibility levels (*E*). The current baseline compliance rates for the four measures are 49 % (blood pressure control), 33 % (LDL control for cholesterol), 35 %, (aspirin recommendation), and 20 % (smoking cessation referral). The number of patients that will be eligible in each 3-month period is based on an average physician roster of approximately 1,000 patients. Currently, 30 % of those patients have hypertension, 30 % have hyperlipidemia, and 20 % smoke. If we make a conservative estimate that 25 % of the patients will have an office visit per 3-month period, each eligible category will range from 50 to 75 patients. In Table 4, we use the lowest (most conservative) assumption of 50 patients, which reflects the likely size of the smoking group. At this level of eligible patients, we will have over 80 % power to detect a 2.2 % change, assuming a starting compliance rate of 20 % (increasing from 20.0 to 22.2 %) and between-site variance of 0.10 on the log scale.

As the number of eligible patients *E* increases, power to detect the same size change increases; for example, with the same effect (a 2.2 % change) there is 92 % power when 70 patients per period have an office visit. This means that we will have increased power for the hypertension, cholesterol, and aspirin measures compared to smoking cessation. In addition, power increases as the baseline compliance rate increases; for example, there is 91 % power to detect a 2.7 % change when the baseline compliance rate is 25 %. Finally, we have little information to estimate the current levels of variation between sites (*σ*
_*d*_^2^). However, the simulations suggest that power does not decrease when the assumed variance is increased from 0.10 to 0.25 on the log scale. If in fact the variance is lower, closer to 0.05, power is increased substantially.
